## Discussion

The main objective of this study is to compare the clinical outcomes of patients undergoing LRS who are managed using different anesthetic protocols. If patients receiving IV lidocaine have a similar postoperative course (intensity of postoperative pain or perioperative complications) as that of patients receiving PV lidocaine, potential complications that are directly associated with this regional blockade technique could be eliminated (e.g., required time, catheter insertion, intrapleural puncture, bleeding, inadequate subdural or epidural injection).

Two main advantages have been proposed for the intraoperative use of local anesthetics in anesthetic regional blocks. One advantage is the effect of blocking the Na^+^ channels on the nerves and the consequent attenuation of the perioperative neuroendocrine response, and the other advantage is the systemic absorption of the local anesthetic into the blood through administration in the PV space, as well as the consequent anti-inflammatory effects that are associated with LA [13]. Blocking Na^+^ channels using local anesthetics does not seem to be related to inflammation control because these effects occur many hours after lidocaine has been metabolized. Furthermore, it has been observed that intravenous lidocaine administration has systemic analgesic properties [23].

Regarding the precautions for the use of IV lidocaine, at high plasma concentrations (5 μg/mL), toxic and undesirable side effects may appear, including overall cardiac effects and central nervous system effects. We do not expect to obtain such high values based on clinical studies that have used even higher doses than in this study [24, 25]. In addition, the study drug will only be used in the operating room under ECG monitoring, and we will not include patients who have liver disease.

Surgeons and anesthesiologists have used many classifications to perform clinical studies comparing the impact of measurements used in the pre-, intra-, or postoperative period. However, the overall impact on the postoperative course has not been taken into account. Most of the studies that analyze PPCs make a composite variable that comprises all the complications that affect the respiratory tract but have very different severity and impact on the postoperative course. For example, the presence of cough, suspicion of infection, pulmonary edema, and subsegmental atelectasis are usually included as PPCs. However, the clinical relevance of these complications is much lower than that of other PPCs, such as pneumonia, lobar atelectasis, or adult respiratory acute syndrome (ARDS). Thus, it is not surprising that there are studies that describe a similar hospital stay between groups despite observing a different incidence of PPCs related to an intervention because certain complications have little effect on the postoperative treatment provided to the patients. This occurs in studies in which all postoperative complications are presented as a single composite variable without taking into account the severity of each of complication. In our research, we want to determine the real impact on the postoperative course of using IV or PV lidocaine. Thus, we will use the C–D classification to rate the postoperative complications and evaluate the intensity of therapeutic measures that are not routinely included within the normal postoperative course.

A limitation of the study is the short-term follow-up of the postoperative inflammatory response. At the pulmonary level, only inflammatory biomarkers will be monitored during surgery, and at the systemic level, this monitoring will be extended up to 24 h postoperatively. The expression of inflammatory mediators varies over time and peaks within hours to days depending on the mediator analyzed. In a previous study, however, we observed a relationship between PPCs and inflammation biomarkers in the same period of time [2]. Another potential limitation of the study is related to the PV administration of ropivacaine at the end of surgery. Patients in the two groups who receive PV saline during surgery will have a lower effective concentration of ropivacaine in the PV space by dilution of local anesthetic in PV space. This suggests a bias for the assessment of analgesia in the first measure performed in the PACU, but we do not think that it will affect measurements taken during the rest of the study.

In this study, we intend to elucidate the role of lidocaine when it is administered using IV or PV routes in the potential attenuation of the systemic inflammatory response, postoperative pain, and other postoperative courses. In addition, by monitoring the levels of lidocaine in the blood, we can estimate whether there is a dose-dependent relationship with the biomarkers of inflammation or other prognostic variables Additional file 1.

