## Abstract

**Background:**

Use of minimally invasive surgical techniques for lung resection surgery (LRS), such as video-assisted thoracoscopy (VATS), has increased in recent years. However, there is little information about the best anesthetic technique in this context. This surgical approach is associated with a lower intensity of postoperative pain, and its use has been proposed in programs for enhanced recovery after surgery (ERAS). This study compares the severity of postoperative complications in patients undergoing LRS who have received lidocaine intraoperatively either intravenously or via paravertebral administration versus saline.

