**Discussion:**

The development of less invasive surgical techniques means that anesthesiologists must adapt their perioperative management protocols and look for anesthetic techniques that provide good analgesic quality and allow rapid rehabilitation of the patient, as proposed in the ERAS protocols. The administration of a continuous infusion of intravenous lidocaine has proven to be useful and safe for the management of other types of surgery, as demonstrated in colorectal cancer. We want to know whether the continuous administration of lidocaine by a paravertebral route can be substituted with the intravenous administration of this local anesthetic in a safe and effective way while avoiding the risks inherent in the use of regional anesthetic techniques. In this way, this technique could be used in a safe and effective way in ERAS programs for pulmonary resection.

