### Interventional treatment

Patients will be recruited consecutively and randomized into three groups of intraoperative management, as follows:
Group 1: Experimental arm—intravenous lidocaine and PV saline (SS). During intraoperative anesthetic maintenance, a continuous IV infusion of lidocaine at 1.5 mg/kg/h will be administered until the end of surgery, and perfusion of 0.9% SS will be administered through an intraoperative PV catheter at a rate of 0.1 mL/kg/h.Group 2: Experimental arm—intravenous SS and PV lidocaine. During anesthesia maintenance, a continuous intravenous infusion of 0.9% SS and an infusion of 2% lidocaine will be administered through an intraoperative PV catheter at a rate of 0.1 mL/kg/h.Group 3: Active comparator—intravenous remifentanil and PV SS. A continuous intravenous infusion of remifentanil will be administered at a rate of 0.1 mg/kg/min during anesthesia maintenance until the end of surgery, and an infusion of 0.9% SS will be administered through an intraoperative PV catheter at a rate of 0.1 mL/kg/ h.

The administration of the study drugs will be stopped immediately in cases where the study participant shows relevant deterioration (e.g., severe hypotension refractory to bolus dose vasoconstrictor treatment, or sudden life-threatening arrhythmia).

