### Postoperative management

After surgery, all patients will be admitted to the postoperative care unit (PACU), where the PV analgesic infusion of 0.2% ropivacaine (0.1 L/kg/h) will be initiated. This PV analgesia will be maintained during the first 48 h after surgery. In the PACU, pain severity will be assessed at rest and during coughing using a numeric rating scale (0 = no pain, 10 = the worst imaginable pain). Furthermore, all patients will be provided with a patient-controlled analgesia pump (PCA) for the self-administration of PV rescue boluses of this solution during the first 48 h postoperatively. If the visual analogic scale (VAS) score is higher than 5 points, an intravenous bolus of 1 mg of morphine will be administered until the VAS reaches a value of less than 5 points.

We will record the number of PV boluses required and administered through the PCA pump within the first 48 h of the postoperative period. We will also record the morphine consumption during this period. Patients will be discharged from the PACU the following morning, except if the responsible physician considers that they should continue to have continuous surveillance.

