##### Secondary outcomes

Secondary objectives including the following will be the comparison between three groups of patients with the following laboratory or clinical data:

Secondary clinical outcomes
Postoperative pain intensity: Postoperative pain will be evaluated using the VAS at rest, during movement, and when coughing during the stay in the PACU and in the two days after. We will also record the doses of self-administered rescue analgesics by PCA pump during the first 48 h after surgery, as well as the cumulative morphine consumption in the first 48 h post-operation.Postoperative pulmonary complications (PPCs): PPCs will be classified using the definition applied in the ARISCAT study [21] (atelectasis, suspected pulmonary infection, respiratory failure, bronchospasm, aspiration pneumonitis, pleural effusion, and pneumothorax; Appendix 2). Because pneumothorax and pleural effusion are the usual outcomes after LRS in the nondependent lung, we will consider them to be complications only if they occur in the dependent lung. The time frame is up to 30 days after intervention.Postoperative cognitive dysfunction (POCD) is defined as the presence of a mini-mental test value less than 27 points at 3 days postoperative (in patients with a value of 30 points on preoperative mini-mental test) or if there is a drop of more than 3 points compared to the value obtained preoperatively (in patients with a mini-mental preoperative test value less than 30 points).The incidence of postoperative surgical complications, which is defined as the presence of any of the complications during the first 30 days postoperatively, as follows:

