### Power calculation

The primary outcome of this clinical trial is the comparison of the proportion of patients included in the different C–D classifications, which indicate the severity of postoperative complications for thoracic surgery. Two comparisons are planned: IV lidocaine + SS-PV vs remifentanyl IV+ SS-PV, and lidocaine PV + SS-IV vs remifentanyl IV+ SS-PV. The sample size is calculated based on the C–D classification ordinal scale. According to a similar study design by our research group, the standard deviation of this scale is approximately 1.5 units. Thus, it is necessary to include 48 patients per group with an alpha risk of 5% and a beta risk of 10% in a two-tailed comparison to detect differences ≥ 1 unit. Because losses are estimated to be 5%, the final sample size should be at least 153 patients (sample size calculator GRANMO version 7.12 April 2012).

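### The article hopes to show that IV lidocaine can replace PV lidocaine, but IV versus PV is neither a planned powered comparison nor given a criterion for similarity, and every arm keeps the PV block

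*Protocol article*

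**What the plan says.** **The aim.** The Discussion paragraph of the Abstract states: "We want to know whether the continuous administration of lidocaine by a paravertebral route can be substituted with the intravenous administration", and adds that the risks of regional techniques would thereby be avoided. The main Discussion gives the inference in conditional form. It begins "If patients receiving IV lidocaine have a similar postoperative course" to patients receiving PV lidocaine, with course described as pain intensity or perioperative complications. It then says that complications tied directly to the block could be eliminated, and lists catheter insertion, intrapleural puncture and bleeding among them.

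**The comparisons.** Power calculation is explicit: "Two comparisons are planned: IV lidocaine + SS-PV vs remifentanyl IV+ SS-PV, and lidocaine PV + SS-IV vs remifentanyl IV+ SS-PV". The sample is sized as a two-tailed comparison to detect at least 1 Clavien–Dindo (C–D) unit. Secondary outcomes "will be the comparison between three groups of patients". Statistical analysis provides ANOVA with post hoc Bonferroni tests, or Kruskal–Wallis with Mann–Whitney tests. No section defines what would count as similar, and no margin is stated.

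**The background treatment.** Under Induction and monitoring, the PV catheter is inserted and a PV ropivacaine bolus is given at closure, without exception by group. The IV lidocaine arm receives saline through its catheter (Interventional treatment). Under Postoperative management, all patients start a PV ropivacaine infusion with PV rescue boluses, and "This PV analgesia will be maintained during the first 48 h after surgery". Intervention plan lists this PV analgesia as common to all patients.

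**The concern.** Two separate gaps lie between the stated aim and the design.

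The first is inferential. To say that one route can replace another, the trial must rule out a meaningful disadvantage of the replacement. The plan sizes only superiority over remifentanil. The IV–PV pair is left to difference tests, and such a test has no outcome that establishes similarity. With no criterion stated, the natural temptation is to read a non-significant result as a similar course.

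The second is structural, and no analysis can repair it. All three arms carry the catheter and receive PV local anesthetic after surgery. The contrast between the lidocaine arms therefore concerns the intraoperative route alone. Pain, one of the two elements of the course that the Discussion names, is measured under PV ropivacaine in every arm for 48 h. Whether patients would do as well with no block is not observed. The limitations paragraph mentions dilution of ropivacaine in the PV-saline arms but not this point.

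At stake is a practice recommendation, to leave out the block in enhanced-recovery programs, that the data could not support.

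**Working it through.** **Inputs.** From Power calculation: SD 1.5 units, two-sided alpha 5%, beta 10%, target difference 1 unit, 48 per group, 5% losses, 153 in total. From Randomization: 1:1:1. From Statistical analysis: Bonferroni as the post hoc adjustment. Like the protocol's own sizing, the check treats C–D grade as a numeric score. The document gives no IV–PV difference or margin, so those values are assumptions shown as a range.

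**1. The plan's own figure.** n per group = 2 × [1.5 × (1.960 + 1.282) / 1]² = 47.3, rounded up to 48. Allowing for losses, 48 / 0.95 = 50.5, rounded up to 51, and 3 × 51 = 153. Both stated figures reproduce. Power at 48 per group for 1 unit is 90.4%.

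**2. Precision for IV minus PV.** SE = 1.5 × √(2/48) = 0.306.
- Unadjusted half-width: 1.960 × 0.306 = 0.60 grade.
- Bonferroni for three pairs (alpha 0.05/3, z = 2.394): 2.394 × 0.306 = 0.73 grade.

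**3. Chance of a non-significant result when IV is truly worse.** P ≈ Φ(z − d/SE).

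| True disadvantage d | d/SE | Unadjusted | Bonferroni, three pairs |
|---|---|---|---|
| 0.50 grade | 1.633 | Φ(0.327) = 63% | Φ(0.761) = 78% |
| 0.75 grade | 2.449 | Φ(−0.489) = 31% | Φ(−0.055) = 48% |

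**4. What a non-inferiority reading could deliver.** Power = Φ(margin/SE − 1.960), with one-sided alpha 2.5% and true difference 0. The last column is the size needed for 90% power, with the three-arm total after 5% losses.

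| Assumed margin | Power with 48 per group | n per group for 90% (total) |
|---|---|---|
| 1.00 | 90% | 48 (153) |
| 0.75 | 69% | 85 (270) |
| 0.50 | 37% | 190 (600) |

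At a margin of 1 unit with the three-pair adjustment, power is Φ(3.266 − 2.394) = 81%.

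**5. The block, arm by arm.**

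| Element | IV lidocaine | PV lidocaine | Remifentanil |
|---|---|---|---|
| PV catheter | yes | yes | yes |
| Intraoperative PV infusion | saline | lidocaine | saline |
| PV ropivacaine bolus at closure | yes | yes | yes |
| PV ropivacaine for 48 h | yes | yes | yes |

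Of these PV elements, only the intraoperative infusion varies. Catheter placement and postoperative PV analgesia are constant, so no contrast in the trial estimates the effect of omitting them.

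**The case against.** The case on the other side has force on several points.

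- **IV versus PV is not wholly absent.** Outcomes are compared across three groups, and the post hoc tests can include this pair. That stands, so it would be wrong to say that the plan contains no such comparison. What is missing is a powered comparison or a criterion for similarity.
- **The main question is sound.** The hypothesis in Background is that lidocaine by either route improves the postoperative course. The two comparisons with remifentanil test it and are correctly sized. The substitution statement is an aim and a conditional, not a reported result. This stands and limits the weight of the point.
- **A common catheter is a reasonable design.** Giving every arm both an IV and a PV infusion serves the double blind, and a shared postoperative analgesic protocol is legitimate. This stands. The defect is the inference drawn from the design, not the catheter.

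A reader might also infer more than the document supports:

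- **That non-significance will be reported as equivalence.** Nothing says so. It is a risk created by leaving similarity undefined.
- **That the lidocaine rates are inconsistent.** The IV arm receives 1.5 mg/kg/h. For the PV arm, "an infusion of 2% lidocaine will be administered through an intraoperative PV catheter at a rate of 0.1 mL/kg/h" works out at 20 mg/mL × 0.1 mL/kg/h = 2.0 mg/kg/h. The document nowhere claims equal dosing, so this contradicts nothing.
- **That the control is misnamed.** The Abstract's Background says "either intravenously or via paravertebral administration versus saline", but the next paragraph of the same Abstract names remifentanil. This wording issue does not bear on IV versus PV.
- **That 1 unit is a ready-made margin because the sample supports it.** It equals the whole difference that the trial is sized to detect. Adopting it for that reason would fit the margin to the sample.

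**Conclusion.** The point holds in this form. The aim of substituting IV for PV lidocaine is not matched by a planned, powered comparison or by any stated criterion for similarity. The inference that block complications could be eliminated does not follow from a design in which every arm keeps the block.

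A null IV–PV test would be weak evidence: the interval extends 0.60 to 0.73 grade either side, and a true 0.5-grade disadvantage would be missed 63% to 78% of the time, depending on whether Bonferroni is applied. These figures rest on the protocol's SD of 1.5, 48 evaluable patients per group and a normal approximation on the C–D score. The structural limit rests on no numerical assumption.

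The comparisons with remifentanil and the sample size of 153 are unaffected. The finding restricts what may be concluded and does not invalidate the trial.

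**What to change.** 1. Prespecify IV versus PV lidocaine as a secondary contrast on C–D grade, reported as an estimate with its 95% confidence interval. State whether the interval is adjusted for multiplicity.
2. State that p > 0.05 for this pair will not be read as similarity.
3. Claim non-inferiority only against a margin justified on clinical grounds and fixed before unblinding. State alongside it that power with 48 per group is 90% at 1 unit, 69% at 0.75 and 37% at 0.5. If no margin can be justified, report the interval alone.
4. Limit the conclusion to intraoperative IV versus PV lidocaine on top of PV ropivacaine in all arms. Drop the inference that block complications could be eliminated, and add the common PV background to the limitations.

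The cost is one added contrast and some rewording, with no extra patients and no change to treatment. The price is a more modest claim: the trial could inform the choice of intraoperative route but not the decision to omit the block.

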## Trial status

After we obtained the approval of the local ethics committee we included the first patient in the study on January 29, 2019. We plan to spend 30 months to include 153 patients and complete the trial in June 2021. Protocol number IGGFGG-2016 version 4.0 27th April 2017.

## Appendix 1

**Table 1 Tab1:** Clavien-Dindo classification

	Grade	Definition
Minor complications	I	Any complication without need for pharmacologic treatment or other intervention
	II	Any complication that requires pharmacologic treatment or minor intervention only
Major complications	III	Any complication that requires surgical, radiologic, endoscopic intervention, or multitherapy
	IIIa	Intervention does not require general anesthesia
	IIIb	Intervention requires general anesthesia
	IV	Any complication requiring intensive care unit management and life support
	IVa	Single organ dysfunction
	IVb	Multiorgan dysfunction
	V	Any complication leading to the death of the patient

## Appendix 2

**Table 2 Tab2:** Definition of postoperative pulmonary complications

Complication	Definition
Respiratory infection	When a patient received antibiotics for a suspected respiratory infection and met at least one of the following criteria: new or changed sputum, new or changed lung opacity, fever, leukocyte count > 12,000/μ
Respiratory failure	When postoperative PaO_2_ < 60 mmHg on room air, ratio of PaO_2_ to inspired oxygen fraction < 300 or arterial oxyhemoglobin saturation measured with pulse oximetry < 90% and requiring oxygen therapy
Pleural effusion	Chest X-ray demonstrating blunting of the costophrenic angle, loss of the sharp silhouette of the ipsilateral hemidiaphragm in upright position, evidence of displacement of adjacent anatomical structures, or (in supine position) a hazy opacity on one hemithorax with preserved vascular shadows
Atelectasis	Lung opacification with a shift of the mediastinum, hilum, or hemidiaphragm toward the affected area, and compensatory overinflation in the adjacent nonatelectatic lung
Pneumothorax	Air in the pleural space with no vascular bed surrounding the visceral pleura
Bronchospasm	Newly detected expiratory wheezing treated with bronchodilators
Aspiration pneumonitis	Acute lung injury after the inhalation of regurgitated gastric contents

## Appendix 3

**Table 3 Tab3:** Spirit figure

Visit	Visit 1 (day − 1)	Visit 2 (day 0)	Visit 3 (day 0)	Visit 4 (day 1)	Visit 5 (day 3)	Visit 6 (discharge)	Visit 7 (30 day)
PLACE	Ward	OR	PACU	Ward/PACU	Ward/PACU	Ward	Medical consulting
Study procedures							
Informed consent	X						
Medical records	X						
Demographic data	X						
Clinical course		X	X	X	X	X	X
Intervention		X					
tests							
Hemogram	X	X	X		X	X	
Gasometry	X	X	X				
Biochemistry	X		X		X	X	
Lidocain blood		X					
Chest X-ray	X		X			X	
ECG	X		X		X		
Mini-mental test	X				X		
Biomarcadores							
BLA		X					
Blood		X	X				
PO events							
Mortality		X	X	X	X	X	X
PO complications			X	X	X	X	X

*OR* operating room, *PACU* postoperative care unit, *BLA* bronchoalveolar lavage, *PO* postoperative

## Abbreviations

AKIN: Acute kidney injury network
APU: Acute pain unit
ARDS: Adult respiratory acute syndrome
BAS: Baseline
Cdyn: Lung dynamic compliance
ECG: Electrocardiography
ERAS: Enhanced recovery after surgery
ICU: Intensive care unit
IL: Interleukin
IV: Intravenous
LA: Local anesthetic
LBA: Bronchoalveolar lavage
LRS: Lung resection surgery
OLV: One-lung ventilation
PACU: Postoperative acute care unit
PCA: Patient controlled analgesia
PEEP: Positive end expiratory pressure
POCD: Postoperative cognitive dysfunction
PPC: Postoperative pulmonary complication
SS: Saline serum
TEA: Thoracic epidural anesthesia
TLV: Two-lung ventilation
TPVB: Thoracic paravertebral block
TV: Tidal volume
VAS: Visual analogic scale
VATS: Video-assisted thoracoscopy
